#### Hemodynamic monitoring

Blood pressure and cardiac output will be measured using the noninvasive NexFin device (Nexfin, Amsterdam, The Netherlands). This is a noninvasive beat-to-beat blood pressure measurement device and cardiac output monitor.

#### Intra-abdominal pressure

Intra-abdominal pressure will be measured every 15 minutes from the retroperitoneal CO_2_ insufflation device.

#### Additional variables

Additional variables will include duration of surgery, drug dosages (propofol, sufentanil, muscle relaxant, reversal agent, atropine, other agents used during anesthesia), duration from reversal to extubation, BIS, and ventilatory variables (tidal volume, respiratory rate, breathing pressure).

### Study measurements in the post-anesthesia care unit

In the recovery room, the following variables will be measured at 15 min intervals: respiratory rate, arterial oxygen saturation, numerical pain rating (on a scale from 0, no pain, to 10, most severe pain imaginable), occurrence of nausea or vomiting, and level of sedation or alertness. The level of sedation/alertness will be assessed in the recovery room using the validated Leiden Observer’s Assessment of Alertness/Sedation (Table 2) [13].

**Table 2 T2:** The Leiden Observer’s Assessment of Alertness and Sedation scale

0	Normal alertness, eyes open, responds normal to command
1	Drowsy with open eyes, closed and opened on command
2	Drowsy with closed eyes, opened in response to light auditory stimulus
3	Eyes closed, opened in response to rubbing the shoulder or a load auditory stimulus
4	Eyes closed and opened only briefly in response to touching the subject
5	Eyes closed, not aroused by touching the subject, aroused by a painful stimulus
6	Not aroused by a painful stimulus

### Economic parameters

Time to optimal extubation conditions from the moment of reversal (with optimal conditions defined as TOF 4 with ratio >90%), time to extubation, duration of surgery, time in the post-anesthesia care unit, and drug consumption will be recorded.

### Safety evaluations

Adverse events (AE) that may occur during the study will be recorded in the case record form. The AE record in the case record form includes the nature of the event (with onset date and time, end date and time), severity, treatment, outcome, and the relationship to the treatment given. All serious AEs will be reported to the medical ethics committee and authorities, as required by the GCP/GRP guidelines.

### Sample size calculation

The sample size calculation is based on the expectations of the surgical rating score during surgery, as provided by an interview with the surgical expert (see Table 3).

**Table 3 T3:** Approximate expectations of SRS for the two treatment arms

**Score**	**Interpretation**	**Treatment group**	
		**Moderate block**	**Deep block**
5	Optimal conditions	10%	70%
4	Good conditions	20%	20%
3	Acceptable conditions	55%	10%
2	Poor conditions	10%	0%
1	Extremely poor conditions	5%	0%

These anticipated frequencies lead to an odds ratio of 21 for obtaining optimal conditions versus suboptimal conditions for deep block as compared with the moderate block condition. To obtain the power for a given sample size, ten thousand simulations were performed with moderate block as a fixed distribution and a simulated distribution of the deep block condition, assuming proportionality of the odds ratio with an odds ratio of 21 and analyzing the results with a proportional odds model using the score test. Results of the simulations are given in Table 4.

**Table 4 T4:** Approximate expectations for the two treatment arms

**Sample size per group (total)**	**Power***
7 (14)	82%
8 (16)	87%
9 (18)	90%
10 (20)	93%
11 (22)	95%
12 (24)	97%

Given uncertainty of the anticipated effect size, a sample size of 12 per group or 24 in total was considered prudent, in order to provide a sufficient margin.

### Statistical analysis

The data analysis will be based on an intention-to-treat approach. For the SRS and other ordinal outcomes, the proportional odds model will be used, using the score test. If the proportionality of odds assumption is systematically violated, the data will be dichotomized for optimal conditions versus nonoptimal conditions. For continuous variables a general linear model will be used. Covariates can be included in these analyses when they provide an improvement of the model (when statistically significant at the 0.05 significance level, two-sided). Covariates to be considered are anesthesia or surgery related (for example, drug dosages, duration of surgery, BIS) and patient related (for example, age, weight, body mass index). Additional analyses will be performed on the secondary outcome parameters. To assess the agreement on the SRS across the various groups of raters the weighted kappa coefficient will be presented.

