Additional secondary endpoints of the study include the effect of depth of NMB on economic parameters (time to optimal extubation conditions (TOF 4 with T1/T4 ratio >90%), time to extubation, duration of surgery, and time in the post-anesthesia care unit), perioperative hemodynamics, and postoperative conditions (respiratory rate, arterial oxygen saturation, pain, sedation).

We hypothesize that:

1. There is a positive association between the depth of NMB and the surgical condition as rated by the attending surgeon.

2. There is a disconnect between the perception of the surgeon and the anesthesiologist in the rating of the surgical conditions.

3. Reversal of a deep NMB with sugammadex leads to postoperative conditions similar or superior to the conditions obtained from reversal of a moderate NMB with neostigmine.

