#### Neuromuscular monitoring

For neuromuscular function monitoring, the TOF-watch SX acceleromyograph (MSD BV, Haarlem, The Netherlands) at the adductor pollicis muscle will be used. The thumb is attached to a flexible adaptor that applies a constant preload to the thumb. Neuromuscular stimulation will be applied to the ulnar nerve via two pediatric electrodes applied on the skin left and right of the ulnar nerve at the distal underarm. Before administration of any neuromuscular blocking agent, but after induction of general anesthesia, the following procedures are conducted to standardize the neuromuscular monitoring: (1) application of a tetanic ulnar nerve stimulation (50 Hz for 5 seconds); (2) calibration of the TOF-watch (CAL 2); (3) performance of a series of TOF measurements, to ensure that the TOF ratio differs by less than 5% between measurements (if the TOF ratio differs by more than 5%, the TOF-watch will be recalibrated). After these steps, the neuromuscular blocking agent according to protocol is administered. When, during the study, the number of measured twitches is zero, the PTC will be measured. A 50 Hz tetanic stimulation for 5 s is followed (after a 3 s rest) by 15 single stimulations at 1 Hz. The number of twitches generated (that is, the PTC) corresponds with the degree of NMB, with a PTC of 1 to 2 reflecting a deep level of NMB.

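### The 0.05 entry rule for covariates leaves baseline adjustment of the secondary hemodynamic endpoint to the data, when the baseline could be pre-specified at the cost of one degree of freedom

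*Protocol article*

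**What the plan says.** - **Endpoint.** The Background section lists perioperative hemodynamics among the additional secondary endpoints.
- **Measurement.** Under Hemodynamic monitoring, blood pressure and cardiac output come from a noninvasive device: "This is a noninvasive beat-to-beat blood pressure measurement device and cardiac output monitor". No start time for recording and no baseline window are given.
- **Model.** Under Statistical analysis: "For continuous variables a general linear model will be used".
- **Entry rule.** The next sentence reads: "Covariates can be included in these analyses when they provide an improvement of the model (when statistically significant at the 0.05 significance level, two-sided".
- **Candidates.** "Covariates to be considered are anesthesia or surgery related (for example, drug dosages, duration of surgery, BIS) and patient related (for example, age, weight, body" (the last item is body mass index). Both groups are introduced as examples, so the list is open. A baseline value of the outcome is neither named nor excluded.
- **Pre-relaxant period.** Under Neuromuscular monitoring, the set-up steps take place "Before administration of any neuromuscular blocking agent, but after induction of general anesthesia". That period is described only for calibrating the neuromuscular monitor.
- **Size.** "a sample size of 12 per group or 24 in total was considered prudent".

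**The concern.** A patient's own starting value is often a strong predictor of later blood pressure or cardiac output, and adjusting for it removes between-patient variation that has nothing to do with the block. The plan's only stated route for a covariate into the model is a significance test on the trial's own data. With 24 patients that test has limited power, so whether the hemodynamic contrast is adjusted could turn on chance, and two equally valid runs of this trial could report differently adjusted estimates. A baseline that always enters the model would fix the estimator in advance and, if the correlation is moderate or high, give a clearly narrower interval.

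**Working it through.** **Inputs from the article.** 12 patients per arm, N = 24 (Sample size calculation); entry level 0.05, two-sided (Statistical analysis).

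**Inputs not in the article, so assumed.** Correlation r between the pre-relaxant value and the later value: 0.3 to 0.8. SD of 15 mmHg, used for one illustration only.

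**1. The plan's own figure.** No SD or power is stated for hemodynamics. The only power figures concern the surgical rating scale. The odds ratio reproduces, (0.70/0.30)/(0.10/0.90) = 21, and simulated power at 12 per group is 96.7% against the stated 97%. Neither bears on this point.

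**2. Unadjusted contrast.** SE = SD × √(2/12) = 0.408 SD. With SD 15 the SE is 6.12 mmHg, and the 95% half-width is 2.074 × 6.12 = 12.7 mmHg (22 df).

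**3. Always adjusted for baseline.** Variance relative to unadjusted = (1 − r²) × (1 + 1/(24 − 4)) = (1 − r²) × 1.05. The factor 1.05 is the cost of estimating the slope.

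**4. Chance that a baseline candidate passes the entry rule.** Fisher's z approximation: P ≈ Φ(atanh(r) × √21 − 1.96).
- r = 0.4: 0.424 × 4.583 = 1.94, less 1.96 = −0.02, about 49%.
- r = 0.5: 0.549 × 4.583 = 2.52, less 1.96 = 0.56, about 71%.
- r = 0.6: 0.693 × 4.583 = 3.18, less 1.96 = 1.22, about 89%.

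Simulation with the arm in the model agrees at 0.5 and 0.6, and gives 29% at 0.3, 98% at 0.7 and nearly 100% at 0.8.

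| Assumed r | 1 − r² | × 1.05 | Variance cut vs unadjusted | Baseline kept under the rule |
|---|---|---|---|---|
| 0.3 | 0.91 | 0.956 | 4% | 29% |
| 0.4 | 0.84 | 0.882 | 12% | 49% |
| 0.5 | 0.75 | 0.788 | 21% | 71% |
| 0.6 | 0.64 | 0.672 | 33% | 89% |
| 0.7 | 0.51 | 0.536 | 46% | 98% |
| 0.8 | 0.36 | 0.378 | 62% | nearly 100% |

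At r = 0 the factor is 1.05, a 5% loss.

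**5. In practical units.** At r = 0.6 and SD 15, the SE is 6.12 × √0.672 = 5.02 and the half-width is 2.080 × 5.02 = 10.4 mmHg (21 df), against 12.7. In patients, 12/0.672 = 17.9 per arm unadjusted would be needed for the same variance. Power for a 1 SD difference is 65% unadjusted, and 67%, 75%, 81% and 89% adjusted at r = 0.3, 0.5, 0.6 and 0.7.

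**6. Which comparison the gains describe.** The variance cuts are against an unadjusted analysis. They apply in full if baseline is never made a candidate. If it is a candidate under the rule, only the trials that drop it are left unadjusted: about 51% at r 0.4, 29% at 0.5, 11% at 0.6 and 2% at 0.7. The average gain over the rule is then smaller than the table shows.

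**7. Chance imbalance.** The baseline difference between arms has SE 0.408 SD, a 95% range of ±0.80 SD, and a 22% chance of exceeding 0.5 SD. At r = 0.6, an imbalance of one SE moves the unadjusted estimate by 0.6 × 0.408 = 0.24 SD in that trial. Over randomizations these shifts average zero.

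**The case against.** The strongest reply is that nothing is fixed wrongly. The covariate list is open, a starting blood pressure fits its patient-related group, and an article may leave the covariates of one secondary endpoint to a fuller document. This stands against one tempting inference, that the plan commits to an analysis without baseline: the text makes no such commitment. It does not dispose of the entry rule, which is stated and covers every covariate. An analysis plan that always included the baseline would have to depart from that sentence.

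Second, a reader might infer that a drug-free baseline is already collected. The article does not say so. It gives no start time for the hemodynamic monitor, and the pre-relaxant interval follows propofol induction and includes a tetanic stimulus, so how well its mean predicts later values is unknown. This stands, and limits the fix.

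Third, a reader might infer that chance imbalance biases the comparison. It does not: the unadjusted test is valid under randomization and its interval already allows for such imbalance.

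Fourth, where adjustment matters most, the rule would usually keep the baseline anyway (98% at r 0.7). This is right, and confines the harm from the rule itself mainly to moderate correlations. It is no help if baseline is never a candidate.

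Finally, none of the three stated hypotheses concerns hemodynamics, and r and the SD are assumptions. Both points stand and keep the importance low.

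**Conclusion.** The point holds in a limited form. The significance rule leaves baseline adjustment of the hemodynamic endpoint to the data, and pre-specifying the baseline is better at almost no cost. The size rests on an assumed correlation: the gain over an unadjusted analysis is material from about 0.5 upward (21% of the variance at 0.5, 46% at 0.7), modest at 0.4 and negligible at about 0.3 or below. The article also names no hemodynamic summary or time point, so the correlation cannot be tied to a defined outcome. The consequence is lost precision and an estimator that is not fixed in advance; it is not bias. The primary surgical rating analysis and the sample size are unaffected. This is a worthwhile refinement of a secondary analysis.

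**What to change.** Add to the analysis plan that, for blood pressure and cardiac output, the baseline is the mean recorded after induction and before the first relaxant dose, and that it enters the hemodynamic general linear models whatever its p-value, as an exception to the 0.05 rule.

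The cost is one degree of freedom (22 to 21) and a variance loss of about 5% if baseline turns out to be unrelated to the outcome. No patients are added. The monitor must be recording before the relaxant is given. The documents do not state this, so it should be confirmed and written down.

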## Abstract

**Background:**

Surgical conditions in laparoscopic surgery are largely determined by the depth of neuromuscular relaxation. Especially in procedures that are confined to a narrow working field, such as retroperitoneal laparoscopic surgery, deep neuromuscular relaxation may be beneficial. Until recently, though, deep neuromuscular block (NMB) came at the expense of a variety of issues that conflicted with its use. However, with the introduction of sugammadex, rapid reversal of a deep NMB is feasible. In the current protocol, the association between the depth of NMB and rating of surgical conditions by the surgeon and anesthesiologist is studied.

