**Methods/design:**

This is a single-center, prospective, randomized, blinded, parallel group and controlled trial. Eligible patients are randomly assigned to one of two groups: (1) deep NMB (post-tetanic count, one or two twitches; *n* = 12) and (2) moderate NMB (train-of-four, 1 to 2 twitches, *n* = 12) by administration of high-dose rocuronium in Group 1 and a combination of atracurium and mivacurium in Group 2. The NMB in Group 1 is reversed by 4 mg/kg sugammadex; the NMB in Group 2 by 1 mg neostigmine and 0.5 mg atropine. Patients are eligible if they are over 18 years, willing to sign the informed consent form, and are scheduled to undergo an elective laparoscopic renal procedure or laparoscopic prostatectomy. A single surgeon performs the surgeries and rates the surgical conditions on a five-point surgical rating scale (SRS) ranging from 1 (poor surgical conditions) to 5 (excellent surgical conditions). The intra-abdominal part of the surgeries is captured on video and a group of five anesthesiologists and ten surgical experts will rate the videos using the same SRS. The primary analysis will be an intention-to-treat analysis. Evaluation will include the association between the level of NMB and SRS, as obtained by the surgeon performing the procedure and the agreement between the scoring of the images by anesthesiologists and surgeons.

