#### Video images

The video images will be collected from the camera connected to the endoscopic probe placed in the retroperitoneal field of surgery. The images collected are the images used by the surgeon to observe the surgical field throughout the procedure (these are his working images). Thus, the collected video images are identical to the image of the surgeon during the procedure. The video images will be edited into short 30-s snippets at 15-min intervals (corresponding with the moment of surgical scoring) plus additional frames from episodes in which sudden changes in surgical conditions occurred. The videos will be rated by surgical experts (five urological surgeons with expertise in laparoscopic surgery, five non-urological surgeons with expertise in laparoscopic surgery) and five anesthesiologists (with expertise in giving anesthesia for laparoscopic procedures). These experts are blinded to the level of NMB and have no knowledge of the study endpoints. The rating score will be identical to the surgical rating score (Table 1).

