An important part of our protocol is the study of the agreement between surgeon and anesthesiologists on the surgical conditions induced by the level of NMB. We do so by having a group of anesthesiologists score the surgical field using the video images obtained during surgery and rated by the surgeon. Since video images are dissimilar to the actual performance of the procedure, we will use a group of surgeons with expertise in laparoscopic surgery as a control group. In our experience, surgeons and anesthesiologists do not always agree on the optimal course of a procedure; this may be partly due to anesthesiologists not always being aware of the impact of anesthesia on the surgical conditions and surgeons not being aware of the impact of anesthesia on the postoperative course of the patient. Our study is aimed to show that under the right conditions the perceived opposing goals of surgeons and anesthesiologists (optimal surgical conditions vs. optimal postoperative conditions) may be met without compromise to one or the other.

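### Weighted kappa, the only statistic named for the surgeon–anesthesiologist disconnect, cannot show its direction or size; add a level-shift contrast on the video ratings

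*Protocol article*

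**What the plan says.** The second hypothesis in the Background section reads: "There is a disconnect between the perception of the surgeon and the anesthesiologist in the rating of the surgical conditions". The clips serve this aim. Five anesthesiologists and ten laparoscopic surgeons rate them on the same five-point SRS that the operating surgeon uses. The Discussion explains the surgeon raters: "Since video images are dissimilar to the actual performance of the procedure, we will use a group of surgeons", who act as a control group.

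The Statistical analysis section names one method for the comparison of raters: "To assess the agreement on the SRS across the various groups of raters the weighted kappa coefficient will be presented". The Methods/design part of the Abstract adds that agreement is to be assessed between the image scores of anesthesiologists and of surgeons.

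On the effect of block depth the text is less uniform. The Background part of the Abstract says that "the association between the depth of NMB and rating of surgical conditions by the surgeon and anesthesiologist is studied". The Methods/design part is narrower: "Evaluation will include the association between the level of NMB and SRS, as obtained by the surgeon performing the procedure". The Statistical analysis section is general: "For the SRS and other ordinal outcomes, the proportional odds model will be used, using the score test". Of the video raters, the Video images section says: "These experts are blinded to the level of NMB and have no knowledge of the study endpoints".

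**The concern.** A disconnect between two specialties can take two quite different forms. Anesthesiologists may rate the same field consistently higher or lower than surgeons, or their ratings may simply scatter more. The first is a difference in standards and has a direction and a size. The second is imprecision. The Background section gives a practical reason to care: a surgeon's request for more relaxation is often not well received by anesthesiologists. Whether they see the field as better than the surgeon does, or merely judge it less reliably, leads to different conclusions.

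Weighted kappa reduces both forms to one number. If it is the only statistic reported, a middling value could be read as a difference in perception when it is scatter, or as fair agreement when one group is consistently a category away.

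**Working it through.** **Inputs (Sample size calculation, Table 3), scores 1 to 5**
- Moderate block: 5, 10, 55, 20, 10%.
- Deep block: 0, 0, 10, 20, 70%.
- Assumption: equal numbers of clips per arm, arms pooled. The average is 2.5, 5, 32.5, 20, 40%, with mean 3.9.

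**The plan's own figures.** The odds ratio for a score of 5 is (0.7/0.3)/(0.1/0.9) = 21, as stated. It is also 21 for a score of 4 or more: (0.9/0.1)/(0.3/0.7). A simulation of the planned score test (two-sided 0.05 assumed) gives power of 81.5, 86.7, 90.6, 93.3, 95.5 and 96.9% for 7 to 12 per group, against 82, 87, 90, 93, 95 and 97% in Table 4. The plan's figures reproduce, and nothing below changes them.

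**Formula.** Weighted kappa = 1 - O/E. O is the mean weighted disagreement observed. E is the same quantity if the two sets of scores were independent with the same margins. The weight is the distance between scores (linear) or its square (quadratic). The article does not say which, so both are shown.

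**Case A: always one category below the surgeon, floored at 1**
- Margin of the lower rater: 7.5, 32.5, 20, 40, 0%, mean 2.925. Mean difference: 2.925 - 3.9 = -0.975.
- Every score except the 2.5% already at 1 is off by exactly one, so O = 0.975 under both weightings.
- Quadratic E = sum of the two variances + squared mean difference = 1.140 + 1.019 + 0.951 = 3.110. Kappa = 1 - 0.975/3.110 = 0.686.
- Linear E = 0.0481 + 0.0538 + 0.2844 + 0.2150 + 0.8300 = 1.431 (one term per surgeon score, 1 to 5). Kappa = 1 - 0.975/1.431 = 0.319.

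**Case B: no shift, a fraction q of scores redrawn at random from the same margin**
- The two margins are identical, so the mean difference is 0.
- O = q × E, hence kappa = 1 - q under either weighting.
- q = 0.314 gives quadratic kappa 0.686; q = 0.681 gives linear kappa 0.319.

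| | Mean difference | Quadratic kappa | Linear kappa |
|---|---|---|---|
| A: constant one-category shift | -0.975 | 0.686 | 0.319 |
| B: 31% redrawn | 0 | 0.686 | – |
| B: 68% redrawn | 0 | – | 0.319 |

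If only half the scores are shifted by one category, the mean difference is -0.49 and kappa is 0.819 (quadratic) or 0.622 (linear). Redrawing 18% or 38% matches these with no mean difference.

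**Limit of case B.** The redraw ignores arm. The arm means are 3.2 and 4.6, so the zero difference holds overall but not within arm: it is +0.7q in the moderate arm and -0.7q in the deep arm. If scores are instead redrawn from their own arm's distribution, the difference is 0 in each arm. The pooled quadratic kappa is then 1 - q × 1.30/2.28, where 1.30 is twice the mean within-arm variance, (0.86 + 0.44)/2 = 0.65, and 2.28 is twice the pooled variance, 1.14. This equals 0.686 at q = 0.55. For linear weights it is 1 - q × 0.775/1.1475, which reaches 0.325 when all scores are redrawn, against 0.319 for the shift. The conclusion does not depend on how the noise is drawn.

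**The case against.** The strongest reply is that kappa fits the aim as worded. The Background section asks whether anesthesiologists can quantify the field and whether the two specialties agree, and hypothesis 2 names no direction. On that reading scatter is itself a failure to agree, and weighted kappa is a standard measure for ordinal scores. The surgeon control group also offers a benchmark: if agreement across specialties is lower than agreement among surgeons, ordinary scoring noise is a less likely explanation. This stands, and it is why kappa should be kept. It still would not show which way or how far the specialties differ.

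A reader might infer more than the article supports:
- *That the video ratings are never compared between arms.* The article does not say so. The SRS sentence in the Statistical analysis section is not confined to the operating surgeon, the video raters use the same scale, and further secondary analyses are announced. What can be said is that this comparison is not explicitly specified, and that the two parts of the Abstract differ on it.
- *That no comparison with the video surgeons is planned.* The Abstract does specify agreement between image scores of anesthesiologists and surgeons, so modality can be held constant.
- *That kappa will be inflated by pooling the arms.* The article does not say whether kappa is pooled or given within arm. Pooling here is an assumption made for the illustration.
- *That the primary outcome lacks blinding.* The operating surgeon is blinded too, according to the Methods and design section.
- *That kappa always hides a one-point shift.* Under linear weights such a shift gives 0.32, which few would call good agreement. The ambiguity there is about the cause. Also, no single redraw fraction in case B matches both weightings at once, so reporting both would help somewhat; the plan names one coefficient.

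Kappa weights and confidence intervals may properly be left to the full protocol or the analysis plan, and their absence from the article is not held against it.

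**Conclusion.** The concern holds in a limited form. The one statistic named for hypothesis 2 measures overall agreement and cannot show the direction or size of a difference between specialties. On the Table 3 distributions pooled 50:50, a nearly full-category shift (-0.975) and scoring with no mean difference yield the same kappa: 0.69 with quadratic weights, 0.32 with linear weights. These values rest on the surgeon's expected distributions, equal pooling and two simplified error processes. They illustrate the ambiguity and do not predict what the trial will find. The point concerns a secondary aim, and it is worth correcting because the ratings needed for a direct answer are already being collected.

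**What to change.** In the Statistical analysis section:

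1. Test hypothesis 2 as the level shift between the anesthesiologists and the video-rating surgeons on the same clips. Use an ordinal model for the clip ratings with rater group and arm as fixed effects and random effects for patient/clip and for rater. Report the shift with its confidence interval. Treat the arm-by-rater-group interaction as exploratory.
2. Keep weighted kappa as a description, within arm as well as overall. Set anesthesiologist–surgeon kappa beside surgeon–surgeon kappa, with patients as the resampling unit.
3. Name the arm effect in the blinded video ratings as a supportive analysis of hypothesis 1, and bring the two parts of the Abstract into line with it.

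The cost is a modest amount of extra analysis, with no new data, raters or procedures. With 24 patients and 15 video raters, precision will be limited, above all for the interaction and the rater variance, and the report should say so.
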